### Study procedures

#### Prior to birth

▪ Prior to the start of the study, health personnel (nurses, pediatricians, and obstetricians) will undergo training regarding: SSC after birth in healthy newborns, human breastfeeding concepts (technical, definition of exclusive lactancy and its effective benefits and contraindications), the institutional human lactation protocol and management of the mothers with their newborn baby▪ The mothers who meet the entry criteria will be identified in the obstetrics and gynecology outpatient department at their prenatal appointment. An obstetric history will be conducted by the physician in order to identify risk factors or conditions that may contraindicate the study. Those mothers who meet the criteria for inclusion will be interviewed in order to explain the purpose of the study, its application and other events to be expected. Should they accept the offer of participation, they will sign an informed consent (Additional file 3) and their personal data, telephone number, and email address will be collected for follow-up▪ Those pregnant women who meet the inclusion criteria and sign an informed consent will be classified randomly using opaque envelopes allocated to the intervention or control group. Each envelope will be coded and assigned a study entry number. Prior to delivery, health professionals can determine what the intervention will be and prepare all their personnel to support the mother and child

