## Methods/design

### Participants, interventions, and outcomes (see: Table 2 Schedule of enrolment, interventions, and assessments)

#### Participants

Included healthy, full-term newborns treated at the Universidad de La Sabana Clinic who meet the following criteria:○ Inclusion criteria:▪ Infants of mothers who prenatally express their desire to breastfeed their newborn baby▪ Full-term newborns who are defined, by obstetric method and confirmed by pediatric method (Ballard), as being between 37 and 42 weeks of gestation with appropriate weight for gestational age (between 10^th^ and 90^th^ percentiles for gestational age)▪ Delivered by vaginal birth▪ Do not require basic or advanced neonatal resuscitation maneuvers▪ Have healthy and stable cardiorespiratory systems at birth▪ Have been permitted to room with the mother
○ Exclusion criteria:▪ Mothers and newborns who present absolute or relative contraindications for human lactancy▪ Multiple pregnancies and births▪ Mothers with postpartum complications that limit the onset of human lactation▪ Major fetal congenital malformations that prevent human lactation

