### Randomization

The 300 newborns will  be randomized using size-6 permuted blocks to ensure that there will be an equal number of participants in the control group and the intervention group. Once the mother signs the informed consent and the entry data for the study has been entered, the operation coordinator of the study will open the opaque envelope, the contents of which determines to which group the mother will be assigned and this information will be recorded immediately in the medical record. The coordinator will verify that the intervention to which the patient was assigned at birth is applied.

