#### Intention-to-treat analysis

All study participants will be analyzed in the group to which they were originally randomized. Loss to follow-up will be analyzed as explained below:

▪ Descriptive analyses﻿ of the lost subjects, will be conducted to determine if they are different from those who continued in the study and whether the losses generated imbalance between the intervention and control groups▪ The effect measure, assuming the worst and best scenario for subjects who were lost to follow-up, will be estimated

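### Women are randomised before birth on criteria that can mostly be settled only at or after birth, which cannot be squared with the stated intention-to-treat set

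*Protocol article*

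**What the plan says.** All references are to the protocol article.

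- **Timing.** Under Prior to birth, eligible mothers are "identified in the obstetrics and gynecology outpatient department at their prenatal appointment", and "Those pregnant women who meet the inclusion criteria and sign an informed consent will be classified randomly using opaque envelopes". Under Randomization, the coordinator opens the envelope once consent is signed and entry data are recorded, and the arm goes straight into the medical record. "Prior to delivery, health professionals can determine what the intervention will be".
- **Unit.** Prior to birth speaks of randomising pregnant women; Randomization speaks of randomising 300 newborns.
- **Eligibility.** Under Participants, the inclusion criteria include vaginal birth, term gestation confirmed by Ballard examination with a weight percentile, cardiorespiratory stability at birth, "Do not require basic or advanced neonatal resuscitation maneuvers" and "Have been permitted to room with the mother". The exclusions include "Mothers with postpartum complications that limit the onset of human lactation".
- **Blinding.** Under Masking, only those who measure results and those who analyse the data are blind.
- **Analysis set.** Under Intention-to-treat analysis, "All study participants will be analyzed in the group to which they were originally randomized". The best-case and worst-case analyses there concern subjects lost to follow-up.

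**The concern.** At a prenatal visit nobody can yet meet most of the inclusion criteria, so some randomised pairs will turn out to be ineligible once the baby is born. The plan then has two options, and each breaks one of its own statements. If the criteria are applied, pairs leave after an allocation that delivery staff can know, and the set analysed is no longer everyone randomised. If nobody leaves, the trial analyses births that fail its entry criteria, some of which could not receive the assigned contact, and the effect is diluted.

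The more serious risk lies with the two criteria that follow treatment. Permission to room in and postpartum complications are settled after SSC can have started, so the assigned arm might influence them. Selecting on them can make the arms differ even if SSC timing has no effect on feeding. Rooming-in also overlaps with a secondary outcome, hospitalisation in the neonatal care unit in the first week: an infant sent there instead of rooming in would fail the criterion and drop out of the outcome it should count towards.

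**Working it through.** **1. When each criterion can be settled**

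| Criterion (Participants) | Settled | Can SSC timing affect it? |
|---|---|---|
| Mother's prenatal wish to breastfeed | Before birth | No |
| Vaginal birth | At birth | No |
| No resuscitation; stability at birth | At birth | Largely no: both arms start with drying and placement on the mother |
| Ballard-confirmed term; weight percentile | After birth | No |
| Permitted to room in | After SSC can have begun | Possibly |
| No postpartum complications (exclusion) | After SSC can have begun | Possibly |

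Five of the six inclusion criteria cannot be settled at the prenatal visit. The weight criterion is also checked at different points. Anthropometry is a mediate intervention in Table 3, done before SSC in the early arm and after it in the immediate arm.

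**2. The plan's sample size**

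Inputs from Sample size: control rate 0.24, RR 1.97 (so 0.24 × 1.97 = 0.4728), two-sided 5%, power 80%, loss 30%, 150 per arm. The pooled two-proportion formula gives 66 per arm, and 66/0.7 rounds up to 95, or 190 in total. The stated 300 is not reproduced. That is a separate matter, but it explains the spare power below.

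Power formula, with n evaluable per arm and p̄ the mean of p1 and p2: Φ{[|p2 − p1| − 1.96√(2p̄(1 − p̄)/n)] / √[(p1(1 − p1) + p2(1 − p2))/n]}. With n = 150 × 0.7 = 105, power is 95%.

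**3. Cost of either reading**

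The article gives no ineligibility rate, so x is assumed to be 10-40%.

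- Exclude: n = 150 × (1 − x) × 0.7, same effect.
- Keep all, no effect in the ineligible: p2 = 0.4728(1 − x) + 0.24x, so RR = 1 + 0.97(1 − x), with n = 105.

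| x | n per arm if excluded | Power at RR 1.97 | RR if all kept | Power at 105 per arm |
|---|---|---|---|---|
| 10% | 94.5 | 92% | 1.87 | 90% |
| 20% | 84 | 89% | 1.78 | 82% |
| 30% | 73.5 | 85% | 1.68 | 72% |
| 40% | 63 | 79% | 1.58 | 59% |

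**4. Bias if removal differs by arm (illustration)**

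Assume no true effect, 24% exclusively breastfed in each full arm, and a rate r of 5-12% among those removed. The rate in those who stay is (0.24 − x·r)/(1 − x).

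- 30% removed in one arm, 20% in the other: 0.321/0.2875 = 1.12 (r = 5%); 0.291/0.270 = 1.08 (r = 12%).
- 40% against 20%: 0.367/0.2875 = 1.28 (r = 5%); 0.320/0.270 = 1.19 (r = 12%).
- Equal removal with the same r in both arms: RR = 1.00.

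**The case against.** A reader might infer that unblinded staff will remove infants and that the intention-to-treat claim is therefore already false. The article does not support that. It states no removal rule and does not say who judges eligibility; its only statement on the point is that everyone is analysed as randomised. Handling of late ineligibility may sit in the full protocol. What stands is that the eligibility list and the analysis statement, as printed, cannot both be followed after prenatal allocation.

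The timing is also less exact than it looks. When entry data are completed is not stated, and the enrolment schedule in Table 2 is not visible. Allocation could fall at admission for delivery. But staff can know the arm before delivery, so allocation still precedes birth and the argument holds.

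Mode of delivery, gestational age and birth weight cannot be changed by SSC, and need for resuscitation largely cannot. Excluding on these, if done alike in both arms, costs numbers and does not bias. That is right, and it confines the bias concern mainly to rooming-in and postpartum complications. The overlap with hospitalisation is partial too: an infant who rooms in may still be admitted later in the first week and be counted.

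The loss of power from exclusion is modest: even 40% ineligible leaves about the planned 80%. That also stands.

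The allocation is "randomized using size-6 permuted blocks", and fixed blocks at one site can be partly predicted by someone who sees every assignment. This matters only if that person also influences who enters, which the article does not say, and consent precedes opening of an opaque envelope. It is a minor point.

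**Conclusion.** The point holds as an internal contradiction: allocation before birth, criteria settled at or after birth, and analysis of everyone as randomised do not fit together. On assumed ineligibility of 10-40% with 30% loss, exclusion takes power at RR 1.97 from about 95% to 92-79%. Retention with no effect in the ineligible takes the RR to 1.87-1.58 and power to 90-59%.

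Bias is possible, not shown. It needs removal that differs by arm or depends on a consequence of treatment, and the spurious RRs of 1.08 to 1.28 above rest wholly on assumed removal rates. It still deserves correction before recruitment, because comparability lost through selective removal cannot be recovered afterwards. The planned best-case and worst-case analyses cover loss to follow-up, not ineligibility.

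**What to change.** Reconcile Participants, Prior to birth, Randomization and Intention-to-treat analysis, and state one unit of randomisation.

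- Keep prenatal identification and consent, but open the envelope as late as practicable before birth (for example on the labour ward when vaginal birth is imminent), once the criteria checkable by then are met.
- Define the intention-to-treat set as every mother-infant pair whose envelope was opened.
- Do not use rooming-in or postpartum complications as grounds for removal after allocation. Report them, and all other ineligibility found at birth, by arm.
- Make any analysis restricted to eligible infants a sensitivity analysis, using only criteria that SSC cannot affect, applied alike in both arms.
- Optionally, vary the block sizes and do not disclose them.

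Late opening does not settle every criterion: resuscitation, stability, Ballard and weight remain unknown until birth. It reduces the number of ineligible pairs, and the definition of the analysis set deals with the rest. The costs are revised wording, envelopes and someone to open them on the labour ward, less notice of the arm for delivery staff, and some dilution from retained infants. Trials status says recruitment is not yet open, so no enrolled participant is affected.

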#### After birth

▪ SSC will be applied according to the assigned group (immediate versus early), and measures of immediate and mediate neonatal adaptation will be applied

##### Prior to discharge

Prior to discharge, the IBFAT instrument will be applied to the mother and her infant by the research monitor and/or operational coordinator.

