**Methods/design:**

A randomized, blind clinical trial will be performed with full-term healthy newborns born at the Universidad de La Sabana Clinic. The blind trial participants will be those persons measuring the results and analyzing the data. The sample size will be calculated for a type I error of 5 %, a two-tailed type II error of 20 %, and an estimated percentage loss of 30 %; 150 infants will be included in each group. Randomization will be performed using permuted, size-6 blocks. Descriptive analysis will be conducted using central tendency and dispersion measurements. A bivariate analysis will be performed to determine which variables are associated with exclusive lactancy at 6 months. For continuous variables, Student’s *t* test will be used for independent samples, and the Wilcoxon rank sum test will be used if the assumptions of normality for the *t* tests are not fulfilled. The assumption of normality will be evaluated using the Shapiro-Wilk and Kolmogorov-Smirnov tests. Categorical variables in contingency tables will be constructed to assess the independence between variables using the chi-square test, or Fisher’s exact test when the assumption of the number of cases is not met by the values in the contingency tables multiplied by two. This will be calculated as a measurement of the effect of relative risk (RR) with confidence intervals; the adjusted measurements will be calculated using a multivariate regression Poisson model. Variables with significant results will be used in the bivariate analysis, and those with biological plausibility will be used for the adjustment. The analysis will be carried out for a two-tailed type I error level of 5 %. The Stata 11 program will be used for data analysis. An interim analysis will be performed upon the submission of half the expected events (106), setting limits for the early termination of the trial according to the method proposed by Pampallona and Tsiatis (1994). Intervention: There will be two SSC randomization groups: early versus immediate. After completing the neonatal adaptation process and based on the group assignment, the mother will be left with her newborn child in hospital accommodation. Prior to discharge, the Infant Breast-Feeding Assessment Tool (IBFAT) will be applied. Monitoring will initially be performed with a face-to-face assessment between 3 and 10 days of life, followed by monthly telephone calls for 6 months to verify lactation status.

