##### Secondary outcomes

Human lactation capacity in the newborn within the first 24 h of life and prior to discharge using the IBFAT scale (Table 4)Maternal satisfaction with breastfeeding in the first 24 h according to the IBFAT scale (Table 4)Evolution of birth weight in the first week of lifeThe need for hospitalization in the neonatal care unit in the first week of life

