### Masking

As to the characteristics of the interventions under evaluation, those who measure the results and who will analyze the data will be blind. To ensure that the blind participant who measures the results will be someone other than the health professional applying SSC, that person will not be in the delivery room and will apply the study measurements to all newborns treated at the clinic without knowledge of whether or not they are study participants.

The person conducting the analysis will be given the database in which the variable that identifies whether the research subject belongs to the control group or the intervention group is found; this will then be coded and the code that identifies them will not be available to the analyst.

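### The coordinator who opens the allocation envelope and checks delivery of the arm may also score the IBFAT, which contradicts the claim that outcome assessors are blind

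*Protocol article*

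**What the plan says.** On who scores the IBFAT, Prior to discharge states that "the IBFAT instrument will be applied to the mother and her infant by the research monitor and/or operational coordinator".

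On who knows the allocation, Randomization states that, after consent and entry of the baseline data, "the operation coordinator of the study will open the opaque envelope". It continues: "The coordinator will verify that the intervention to which the patient was assigned at birth is applied".

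On blinding, the Methods/design part of the abstract says: "The blind trial participants will be those persons measuring the results and analyzing the data". The Masking section repeats that "those who measure the results and who will analyze the data will be blind". It also says how this is to be achieved: the assessor is not the professional who applies skin-to-skin contact and stays out of the delivery room. This person "will apply the study measurements to all newborns treated at the clinic without knowledge of whether or not they are study participants".

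On the role of the instrument, the first item under Secondary outcomes is "Human lactation capacity in the newborn within the first 24 h of life and prior to discharge using the IBFAT scale". The second is maternal satisfaction from the same form. Feeding competence on the IBFAT is also the first of the Specific objectives.

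**The concern.** The sections on procedures and on masking cannot both be followed if the coordinator scores an infant. The coordinator knows that the mother is in the trial and which arm she is in, whereas the Masking section requires an assessor who does not know even that she is in the trial.

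This matters because of how the IBFAT is graded. In Table 4, readiness to feed, rooting and sucking each rest on the observer's judgement of how much help or stimulation the infant needed, or how well it performed. Fixing is tied to the recorded time to latch and leaves less room for opinion. Satisfaction is the mother's own answer, but the assessor asks for it. An assessor who knows the arm and expects one start time to do better can tilt such grades without intending to. The article does not describe mothers or delivery staff as masked, so assessor masking is the main stated protection for these outcomes.

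**Working it through.** **Step 1. Compare the roles.**

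| Requirement for the assessor (Masking) | Operational coordinator (Prior to discharge, Randomization) |
|---|---|
| Does not know the arm | Opens the envelope that gives the arm, then verifies that this arm is delivered |
| Does not know who is a participant | Opens the envelope after that mother has consented and her entry data are in |
| Measures outcomes | Named as one of two roles that may apply the IBFAT |

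The first two rows cannot be met by someone with the coordinator's duties. One section writes operational coordinator and the other operation coordinator of the study. Nothing in the article separates them, and one role is the natural reading.

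**Step 2. Which outcomes are touched.** The IBFAT feeds the first two secondary outcomes. The primary outcome, exclusive lactation for three or more months, comes from monthly telephone calls. The Follow-up section does not say who makes them, so the contradiction does not extend to the primary outcome on this text.

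**Step 3. A worst-case size.** The plan gives no figure to reproduce, and the contradiction itself needs none. The arithmetic below only shows a scale.

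- From Table 4: items 2 to 5 are scored 0 to 3, so the maximum is 4 × 3 = 12. Item 1 carries no points, and item 6 (satisfaction) is outside the score.
- From Sample size: 150 infants per arm.
- Assumed: SD of 2 to 3 points (the article gives none), and a bias of one category on one item in every infant of one arm, with no true difference.
- Shift: 1 point, 1/12 = 8% of the scale. Standardised: 1/3 = 0.33 SD to 1/2 = 0.5 SD.
- Standard error of the difference = SD × √(2/150). SD 3: 0.346. SD 2: 0.231.
- Chance of a significant result at two-sided 5% = Φ(shift/SE − 1.96). SD 3: Φ(2.89 − 1.96) = Φ(0.93) = 0.82. SD 2: Φ(4.33 − 1.96) = Φ(2.37) = 0.99.

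If the coordinator scores a fraction f of the infants, the mean shift is f × 1 point. With f = 0.5 it is 0.5 points, or 0.17 to 0.25 SD. The chance of a significant result is then Φ(1.44 − 1.96) = 0.30 for SD 3 and Φ(2.17 − 1.96) = 0.58 for SD 2. With f = 0 there is no bias from this source.

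**The case against.** The strongest reply is that the wording is permissive. The monitor alone may do all the scoring, and then the Masking section is respected. That is true, and it means that unblinded scoring is allowed rather than certain. But the sentence equally allows the coordinator to score alone, and a blinding claim made without condition cannot rest on a procedure that permits the opposite.

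Three further points stand and limit the concern:

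- The size is a worst case. The SD is assumed, the shift requires the coordinator to score every infant, and an infant already at 3 on an item cannot be raised.
- Not every part of the form is equally open to bias. Fixing is timed, and a blind interviewer would only partly protect satisfaction, since the mother is not claimed to be blind.
- The research monitor is not stated to be blind either. Taking out the coordinator does not by itself produce a blind assessor.

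A reader might also infer that discharge and first-week staff will see the arm, because Randomization says that "this information will be recorded immediately in the medical record". The article does not say that these staff consult that entry, and shielding the record is a detail that a condensed article may leave to the full protocol. Chart access is therefore no part of this point.

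**Conclusion.** The contradiction is real and lies in the printed text, so a fuller document could not remove it by adding detail. As written, the IBFAT may be scored by someone who knows the allocation, while the abstract and the Masking section say that this cannot happen.

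Its reach is limited to the IBFAT secondary outcomes, mainly feeding capacity and less so satisfaction. A reader might infer that the trial's main result is compromised. The documents do not support that, because nothing places the coordinator on the telephone follow-up.

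The possible bias runs from none, if the monitor scores every infant and is in fact blind, to a worst case of 0.33 to 0.5 SD under the assumed SD and a uniform 1-point shift. The conclusion rests on reading the two coordinator titles as one role.

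**What to change.** In Prior to discharge, delete the coordinator from those who may apply the IBFAT. Add that it is applied only by an assessor, such as the research monitor already named, who has no role in randomization, in verifying delivery of the arm or in handling the allocation record, and who does not consult the recorded allocation before scoring. The restriction has to be written on the assessor's role, because naming the monitor alone would not establish blinding.

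Moving the allocation to a sealed log is not needed and would fit poorly with Prior to birth, where health professionals can learn the assignment before delivery so as to prepare.

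If the coordinator must remain a possible scorer, withdraw the assessor-blinding claim for the IBFAT in the abstract and the Masking section.

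The cost is a short wording change and slightly less scheduling flexibility before discharge. Trials status says that recruitment has not opened, so the change can be made before any infant is scored.
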